**Table 1: Adverse Event Management**

| **Adverse Event** | **Subject Management** |
| --- | --- |
| Hypertension | - Elevated systolic blood pressure (>180 mm Hg and/or elevated diastolic blood pressure (>120 mm Hg at one or more time-point) with no other symptoms will be re-checked in 10 minutes. - If the acute elevation of blood pressure continues, hydralazine 25mg will be administered to the subject. - If other physical symptoms are present, blood pressure will be re-checked immediately and the licensed physician will decide the appropriate level of care, whether through medication administration or having the subject escorted to the University of Utah Emergency Department. |
| Headache | - Subjects will be examined by a licensed physician and offered acetaminophen 650mg |
| Tachycardia | - Elevated heart rate (100 – 160 bpm) noted on vital sign monitoring will first be met with therapeutic interactions with the therapist given the likelihood of this being secondary to the subject’s experience. This will continue to be monitored, with a licensed physician examining the subject if the heart rate continues to be elevated. - Elevated heart rate (>160 bpm) will prompt examination by a licensed physician who will examine the subject and triage appropriately whether the subject should receive propranolol 10mg and/or be escorted to the University of Utah Emergency Department. |
| Nausea/Vomiting | - Subjects will be assessed by a licensed physician with an emphasis on the least invasive means, avoiding medication administration if possible. - If nausea/emesis is significant and subject requesting antiemetic, promethazine 25mg will be provided. |
| Other | - A licensed physician will examine the subject and determine the appropriate level of care for the subject |

## Contraception

Non-clinical and clinical data describing the effects of oral psilocybin on lactation, sperm, and teratogenicity are not available. Therefore, women of childbearing potential should have a negative pregnancy test at the time of screening and use a highly effective form of contraception for the duration of study participation and for at least one month after psilocybin administration.

Male subjects should be instructed to use a condom for 24 hours after the psilocybin dose.

Acceptable highly effective contraceptive methods include:

- - Bilateral tubal occlusion
  - Vasectomized partner
  - Intra-uterine device (IUD) or hormone-releasing system (IUS)
  - Any hormonal (estrogen combined with progesterone or progesterone alone) contraception associated with inhibition of ovulation: implanted, oral, intravaginal, transdermal, or injectable.
  - The combination of a barrier method with spermicide (i.e., diaphragm, sponge, or male or female condoms).
  - Abstinence from heterosexual intercourse.

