**Yes/No Eligibility Questions (Response of “no” = subject ineligible)**

- PHQ-9 score ≥ 10 and meet DSM-5 criteria for a depressive disorder, including adjustment disorder with depressed mood.
- Meet our working definition of burnout which will involve a score on the emotional exhaustion subscale (≥ 27) and a ‘high’ score on one other subscale (either depersonalization ≥ 13 or personal accomplishment ≤ 21).
- Not taking regularly scheduled medications to treat depression and/or anxiety, including benzodiazepines, for at least 4 weeks prior to administration of psilocybin, if randomized to that study arm.
- Fluent in English.
- Reading literacy and comprehension sufficient for understanding the consent form and study questionnaires, as evaluated by study staff obtaining consent.
- Able to provide informed consent and willing to sign an approved consent form that conforms to federal and institutional guidelines.
- ECOG Performance Status ≤ 2.
- Have a support person that would be able to escort the subject home on the evening of the psilocybin dosing session. The use of ride services will not be permitted (e.g., Uber, Lift, taxi, etc.)
- (If randomized to psilocybin arm) Adequate liver function as defined as:
  - Total Bilirubin < 1.5x institutional upper limit of normal (ULN) unless elevated bilirubin is related to Gilbert’s Syndrome.
  - AST(SGOT)/ALT(SGPT) <3 x institutional ULN
  - For female subjects: Negative pregnancy test and agreement to use highly effective contraception or evidence of post-menopausal status if randomized to psilocybin arm. The post-menopausal status will be defined as having been amenorrheic for 12 months without an alternative medical cause.
  - For male subjects: agree to condom use during intercourse for 24 hours post-psilocybin dose.
  - Agree to refrain from using any psychoactive drugs, including alcoholic beverages, ondansetron, cannabis, and non-routine PRN medications within 24 hours of the psilocybin administration. Exceptions include daily use of caffeine, nicotine, and opioid pain medication.
  - Agree that for one week preceding the psilocybin session, he/she will refrain from taking any nonprescription medication, nutritional supplement, or herbal supplement except when approved by the research team. Exceptions will be evaluated by the research team and will include acetaminophen, non-steroidal anti-inflammatory drugs, and common doses of vitamins and minerals.

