### MBSR+PAP Arm

Participants randomized to the MBSR + PAP arm will participate in the same curriculum as described above, however, will substitute a group PAP session instead of the group MBSR retreat. The PAP intervention will be facilitated with a 1:1 therapist/participant ratio with an additional lead therapist. Group size will be determined by ease of recruitment but will be no fewer than 2, and no more than 6 participants per PAP session. The group will be overseen by a lead therapist who will be available through the entirety of the dosing session and will not be assigned to any one individual participant. Timing of the PAP session will be during the MBSR curriculum with a goal of scheduling at same time as the MBSR retreat for the other arm. However, scheduling will be flexible depending on participant schedules, particularly given working demands of healthcare providers amid a pandemic: this session may occur before or after the group meditation retreat +/- 1 week. The psilocybin session will be accompanied by 3 preceding group preparatory sessions of 90 minutes each (one of these can be via Zoom per participant) as well as 3 integration sessions of 90 minutes each (up to two of these can be via Zoom per participant). Participants must continue to meet all inclusion criteria as well as hepatic and renal function requirements laid out in inclusion and exclusion criteria to receive psilocybin.

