| Challenging Experience Questionnaire |  |  |  |  |  |  |  |  | x |  |  |  |  |
| Nondual Awareness Dimensional Assessment (state) |  |  |  |  |  |  |  |  | x | **x** |  |  |  |
| Nondual Awareness Dimensional Assessment (trait) |  |  | **x** |  |  |  |  |  |  |  |  | **x** |  |
| Watts’ Connectedness Scale |  |  | x |  |  |  |  |  |  |  |  | x | **x** |
| Toronto Mindfulness Scale, FFMQ-15 |  |  | x |  |  |  |  |  |  |  |  | x | **x** |
| Brief Savoring Inventory |  |  | x |  |  |  |  |  |  |  |  | x |  |
| **Storyline Health Questionnaires** |  |  |  |  |  |  |  |  |  |  |  |  |  |
| **Storyline Integrative Assessment**: Neurological, Psychiatric, Cognitive, Psychological |  |  | x |  |  |  |  |  |  |  |  | x | **x** |
| Qualitative assessment on workplace functionality ^vii.^ |  |  | x |  |  |  |  |  |  |  |  | x |  |
| Qualitative assessment on relationship between mindfulness training and psilocybin session and group format ^x^ |  |  |  |  |  |  |  | **x** |  |  |  | x |  |
| **Safety** |  |  |  |  |  |  |  |  |  |  |  |  |  |
| CTCAE Adverse Event collection^[[6]](#endnote-6)^ | x |  | x |  | x |  | x | x | x | x | x | x | **x** |
| Assess suicidality: C-SSRS ^x^ | x |  |  |  |  |  |  | x |  | x | x | **x** | **x** |
| Assess concomitant meds | x |  | x |  | x |  | x | x | x | x | x | x | **x** |

^i.^ Follow up measures to be administered 14 days (+/- 3) and 180 days (+/-7) after final MBSR session in week 8.

^ii.^ Vital signs include systolic and diastolic blood pressure, heart rate, respiratory rate, pulse oximetry, weight. Weight captured at screening only.

^iii.^ Pregnancy test (serum or urine) must be obtained at screening and ≤ 8 days prior to psilocybin administration for all women of childbearing potential and as clinically indicated while on trial.

^iv.^ On day of psilocybin administration vital signs will be assessed approx. 10 min before dosing and at 30, 50, 90, 120, 180, 240, 300, and 360 minutes after psilocybin administration. The baseline vitals will be allowed a 60-minute window to collect prior to dosing, while each subsequent vital collection will be allowed a window of +/- 15 minutes.

^v.^ All Questionnaires scheduled for MBSR Week 1 to be administered prior to the first MBSR session. Questionnaires and safety measures assessed similarly across both study arms.

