## Laboratory Assessments

Samples for all laboratory assessments will be drawn at the time points indicated in the Schedule of Events and when clinically indicated. All safety laboratory analyses will be performed by the local laboratory. All safety laboratory assessments must be reviewed by the treating investigator prior to study drug administration. When applicable, results from the pregnancy test must also be available for review prior to dosing. Laboratory screening will only be required for participants randomized to the MBSR + PAP arm to ensure safe and effective administration of study drug.

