## Reporting of Pregnancy

Although pregnancy is not considered an adverse event, any exposure to the investigational products during pregnancy or breastfeeding must be reported promptly. Exposure may occur by a woman actively receiving study therapy. Any possible pregnancy or breastfeeding exposure during study therapy and up to 30 days after the last dose of psilocybin must be reported within one business day of awareness regardless of the occurrence of an SAE. Should a woman on study therapy become pregnant, she should immediately discontinue study treatment.

Women exposed to IP during pregnancy or while breastfeeding will be followed for pregnancy outcome and neonate health. Pregnancy outcomes may meet criteria as an SAE if ectopic pregnancy, spontaneous abortion, intrauterine fetal demise, neonatal death, or congenital anomaly occurs. Congenital anomalies that occur in a live-born baby, a terminated fetus, an intrauterine fetal demise, or a neonatal death should be reported as an SAE. Any neonatal deaths that occur up to 30 days after birth or breastfeeding exposure should be reported as an SAE. All live births must be followed for a minimum of 30 days or to the first well-baby visit. Further follow-up on birth outcomes and neonate health will be handled on a case-by-case base.

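### Missing lactation data are given as a reason for precautions, but no specific eligibility, discontinuation, schedule or pre-dose item covers breastfeeding

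*Protocol*

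**What the plan says.** Section 7.2 (Contraception) gives the reason for its precautions: "Non-clinical and clinical data describing the effects of oral psilocybin on lactation, sperm, and teratogenicity are not available". For women of childbearing potential it then requires a negative pregnancy test at screening and highly effective contraception during the study and "for at least one month after psilocybin administration". For men it requires a condom for 24 hours.

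Breastfeeding appears in the visible protocol only in section 15.7 (Reporting of Pregnancy): "Any possible pregnancy or breastfeeding exposure during study therapy and up to 30 days after the last dose of psilocybin must be reported". The deadline for that report is one business day. The same section adds: "Women exposed to IP during pregnancy or while breastfeeding will be followed for pregnancy outcome and neonate health".

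Pregnancy is handled specifically at each step:

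- Section 5.1, among the psilocybin-arm items: "For female subjects: Negative pregnancy test and agreement to use highly effective contraception or evidence of post-menopausal status if randomized to psilocybin arm".
- Section 8, footnote iii: a test "must be obtained at screening and ≤ 8 days prior to psilocybin administration for all women of childbearing potential".
- Section 10.5: "When applicable, results from the pregnancy test must also be available for review prior to dosing".
- Section 6.4 lists pregnancy as a reason to discontinue treatment, and section 15.7 repeats this.

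Before dosing, section 6.1 (MBSR+PAP Arm) says: "Participants must continue to meet all inclusion criteria as well as hepatic and renal function requirements".

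**The concern.** Section 7.2 names three areas without data and then sets precautions. Teratogenicity is met by pregnancy testing and contraception, and sperm by condom use. Lactation has no matching measure.

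A negative pregnancy test does not identify a woman who is breastfeeding. A breastfeeding woman who uses contraception therefore passes every specific check relevant to this risk. She could be dosed unless someone happens to learn of it and acts. The person at risk is an infant who is not a participant, exposed to a drug for which the protocol says there are no lactation data. The report required by section 15.7 comes after the event. It also depends on the exposure being noticed, because no scheduled item asks about it.

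**Working it through.** No figure in the plan needs reproducing. The check sets pregnancy and breastfeeding side by side, and then looks at the durations that bear on the remedy.

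**1. Specific controls**

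| Place in protocol | Pregnancy | Breastfeeding |
|---|---|---|
| 5.1 Inclusion | Negative test; contraception or menopause | None |
| 5.2 Exclusion | (covered in 5.1) | None |
| 6.1 Pre-dose re-check | Through the inclusion criteria | None, as no criterion exists to re-apply |
| 6.2 Pre-dose instructions, 6.3 Prohibited Therapy | Not mentioned | Not mentioned |
| 6.4 Discontinuation list | Listed | Not listed |
| 7.2 Precautions | Test and contraception | None |
| 8 Schedule and footnotes | Two tests | None |
| 9.4 Preparatory and dosing sessions | Not mentioned | Not mentioned |
| 10.5 and Table 3 | Result available before dosing | None |
| 15.7 Reporting | Report, follow up, discontinue | Report and follow up only |

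**2. Non-specific routes**

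- Medical history and physical examination at screening (sections 8 and 10.1), and the contraception or menopause discussion under 5.1, could bring breastfeeding to light.
- The investigator could then use the general safety exclusion that closes section 5.2, whose listed examples do not include breastfeeding, or withdraw the participant for safety under section 6.4.
- Section 5 requires eligibility to hold up to the first group therapy session, while section 8 places dosing in week 7. The re-check in section 6.1 refers to the inclusion criteria and to liver and kidney requirements. It does not expressly re-apply the general exclusion.

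**3. Durations in the protocol**

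- Section 3.1: psilocin half-life about 3 ± 1.1 hours; detectable for up to 24 hours.
- Section 5.2 uses at least five half-lives as the washout for prohibited medicines. Applied to psilocin: 5 × 3 = 15 hours. With the half-life at 3 + 1.1 = 4.1 hours: 5 × 4.1 = 20.5 hours. Both lie inside the 24 hours of detectability.
- Section 15.7: 30 days × 24 = 720 hours, and 720 / 24 = 30 times the detectability limit.

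These are not milk data, so they do not fix an interruption period. They do show that the 30 days is a reporting window and should not be read as a measured exposure window.

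**4. Where a criterion would sit**

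The psilocybin-arm items in 5.1 apply only after allocation to that arm, and section 10.5 limits laboratory screening to the same participants. A breastfeeding criterion placed there could lose a woman after randomization, from one arm only. One of 12 is 1/12 = 8.3% of that arm, and she would remain in the intention-to-treat set under section 12.1.

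**The case against.** The strongest reply is that the risk is already partly covered. The general exclusion in 5.2 is itself a listed criterion, an investigator signs the eligibility certification, history and examination are taken at screening, and every participant is a physician or nurse. This stands to a degree: it would be wrong to say that a breastfeeding woman meets every criterion. She meets every specific one, and whether she is dosed then depends on an unprompted disclosure and a discretionary judgment. For pregnancy the protocol did not rely on discretion.

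A second reply is that consent text and the Investigator's Brochure are not visible and may address breastfeeding. That is possible, and it limits the finding to the visible protocol. It would not put an item in the eligibility checklist, which is shown.

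Two stronger readings are tempting, and the document supports neither. A reader might infer that sections 7.2 and 15.7 contradict the eligibility criteria, or that the protocol means to dose breastfeeding women. The reporting rule would be needed even with an exclusion in place, so this is an omission. A reader might also take the 30 days in section 15.7 as the period of risk to the infant; the document gives it only as a reporting period.

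**Conclusion.** The gap is real and modest. The protocol identifies lactation as an area without data, sets no preventive measure for it, and deals with breastfeeding only after exposure. It affects women among the 12 participants planned for the psilocybin arm (section 4.2), each receiving a single 25 mg dose. The document does not say how many might be breastfeeding; the number may be zero, and none is estimated here. The stake is infant safety. Sample size, endpoints and analysis are untouched. The conclusion assumes that no unseen document adds a binding eligibility or pre-dose check. It merits a cheap improvement to the protocol.

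**What to change.** Add to section 5.1 a criterion decided for all women at screening, before randomization: *Not breastfeeding, or agrees, if allocated to psilocybin, to stop breastfeeding and discard milk from dosing for a period stated in the protocol.*

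- **Period.** The sponsor's physicians should set it with reference to the elimination data in section 3.1, recognising that these are plasma data and not milk data. It should not default to 30 days.
- **Section 15.7.** State whether breastfeeding resumed within the 30 days is still reportable.
- **Pre-dose check.** Re-ask and record the answer before dosing; section 6.1 already re-applies the inclusion criteria at that point. Give the question its own stated time. The pre-dose pregnancy test cannot serve as the anchor as written, because section 8 allows it up to 8 days before dosing and Table 3 sets it within 24 hours.
- **Section 7.2.** Repeat the rule there.

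The cost is one checklist line and one recorded question asked twice. An occasional candidate who will not interrupt breastfeeding would be lost before randomization, where it does not unbalance the arms. A participant who starts breastfeeding or changes her mind before dosing could still be lost afterwards.

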# SCHEDULE OF EVENTS

The Schedule of Events table provides an overview of the protocol visits and procedures. Refer to the Study Assessments and Procedures section of the protocol for detailed information on each assessment required for compliance with the protocol. The investigator may schedule visits (unplanned visits) in addition to those listed in the Schedule of Events table in order to conduct evaluations or assessments required to protect the wellbeing of the subject. This Schedule of Events will be followed for the entire study.

**Table 2: Schedule of Events**

| **Week** | **-5 to -1** | | **1** | **2** | **3** | **4** | **5** | **6** | **7** | **8** | **9** | **11** | **33** |
| --- | --- | --- | --- | --- | --- | --- | --- | --- | --- | --- | --- | --- | --- |
| **Day** | **-35 to -7** | | **0-7** | **8-14** | **15-21** | **Etc.** |  |  |  |  |  |  |  |
| **Study Stage** | **Screen** | | **Active** | | | | | | | | | **Follow-up^[[1]](#endnote-1)^** | |
| Informed consent, registration | x |  |  |  |  |  |  |  |  |  |  |  |  |
| Eligibility criteria | x |  |  |  |  |  |  |  |  |  |  |  |  |
| Demographics | x |  |  |  |  |  |  |  |  |  |  |  |  |
| Medical History | x |  |  |  |  |  |  |  |  |  |  |  |  |
| Vitals and PE^[[2]](#endnote-2)^ | x |  |  |  |  |  |  |  |  |  |  |  |  |
| Randomization/assignment | **x** |  |  |  |  |  |  |  |  |  |  |  |  |
| Expectancy Questionnaires |  | **x** | **x** |  |  |  |  |  |  |  |  |  |  |
| **MBSR ARM** |  |  | **1** | **2** | **3** | **4** | **5** | **6** | **7** | **8** | **9** | **11** | **33** |
| **MBSR course** |  |  | **x** | **x** | **x** | **x** | **x** | **x** | **x** | **x** |  |  |  |
| **Retreat** |  |  |  |  |  |  |  |  | **x** |  |  |  |  |
|  |  |  |  |  |  |  |  |  |  |  |  |  |  |
| **PAP-MBSR** |  |  | **1** | **2** | **3** | **4** | **5** | **6** | **7** | **8** | **9** | **11** | **33** |
| Comprehensive Metabolic Panel ^xi.^ |  | x |  |  |  |  |  |  |  |  |  |  |  |
| Urine drug screen |  | **x** |  |  |  |  |  | x (within 24 hrs) |  |  |  |  |  |
| Pregnancy test ^iii^ |  | x |  |  |  |  |  | x (within 8 days of PAP) |  |  |  |  |  |
| MBSR Course |  |  | **x** | **x** | **x** | **x** | **x** | x | x | **x** |  |  |  |
| Prep Sessions 1-3 |  |  |  |  |  |  | **x** | x |  |  |  |  |  |
| PAP Session |  |  |  |  |  |  |  |  | x |  |  |  |  |
| Vitals monitoring |  |  |  |  |  |  |  |  | **x^[[3]](#endnote-3)^** |  |  |  |  |
| Integration Sessions 1-3 |  |  |  |  |  |  |  |  | **x** | **x** | **x** |  |  |
| **Assessments** |  |  | **1^[[4]](#endnote-4)^** | **2** | **3** | **4** | **5** | **6** | **7** | **8^[[5]](#endnote-5)^** | **9** | **11** | **33** |
| PHQ-9 | x |  |  |  |  |  |  |  |  |  |  |  |  |
| MBI-HSS (MP) | x |  | x |  |  |  |  |  |  |  |  | x | **x** |
| QIDS-SR-16 |  |  | x |  |  |  |  |  |  |  |  | x | **x** |
| Demoralization II scale |  |  | x |  |  |  |  |  |  |  |  | x |  |
| PTSD Checklist 5 |  |  | x |  |  |  |  |  |  |  |  | x | **x** |
| MEQ-30 |  |  |  |  |  |  |  |  | x |  |  |  |  |
| Challenging Experience Questionnaire |  |  |  |  |  |  |  |  | x |  |  |  |  |
| Nondual Awareness Dimensional Assessment (state) |  |  |  |  |  |  |  |  | x | **x** |  |  |  |
| Nondual Awareness Dimensional Assessment (trait) |  |  | **x** |  |  |  |  |  |  |  |  | **x** |  |
| Watts’ Connectedness Scale |  |  | x |  |  |  |  |  |  |  |  | x | **x** |
| Toronto Mindfulness Scale, FFMQ-15 |  |  | x |  |  |  |  |  |  |  |  | x | **x** |
| Brief Savoring Inventory |  |  | x |  |  |  |  |  |  |  |  | x |  |
| **Storyline Health Questionnaires** |  |  |  |  |  |  |  |  |  |  |  |  |  |
| **Storyline Integrative Assessment**: Neurological, Psychiatric, Cognitive, Psychological |  |  | x |  |  |  |  |  |  |  |  | x | **x** |
| Qualitative assessment on workplace functionality ^vii.^ |  |  | x |  |  |  |  |  |  |  |  | x |  |
| Qualitative assessment on relationship between mindfulness training and psilocybin session and group format ^x^ |  |  |  |  |  |  |  | **x** |  |  |  | x |  |
| **Safety** |  |  |  |  |  |  |  |  |  |  |  |  |  |
| CTCAE Adverse Event collection^[[6]](#endnote-6)^ | x |  | x |  | x |  | x | x | x | x | x | x | **x** |
| Assess suicidality: C-SSRS ^x^ | x |  |  |  |  |  |  | x |  | x | x | **x** | **x** |
| Assess concomitant meds | x |  | x |  | x |  | x | x | x | x | x | x | **x** |

^i.^ Follow up measures to be administered 14 days (+/- 3) and 180 days (+/-7) after final MBSR session in week 8.

^ii.^ Vital signs include systolic and diastolic blood pressure, heart rate, respiratory rate, pulse oximetry, weight. Weight captured at screening only.

^iii.^ Pregnancy test (serum or urine) must be obtained at screening and ≤ 8 days prior to psilocybin administration for all women of childbearing potential and as clinically indicated while on trial.

^iv.^ On day of psilocybin administration vital signs will be assessed approx. 10 min before dosing and at 30, 50, 90, 120, 180, 240, 300, and 360 minutes after psilocybin administration. The baseline vitals will be allowed a 60-minute window to collect prior to dosing, while each subsequent vital collection will be allowed a window of +/- 15 minutes.

^v.^ All Questionnaires scheduled for MBSR Week 1 to be administered prior to the first MBSR session. Questionnaires and safety measures assessed similarly across both study arms.

^vi.^ Integration sessions #1 and #2 both included in this week for the PAP + MBSR arm. Adverse event collection, suicidality, concomitant meds will all be assessed x 2 during this week for the PAP+MBSR arm.

^vii.^ This will consist of a 3-minute free-form video recorded response on the Storyline platform by participants regarding perceived functioning in the workplace.

^viii.^ This will consist of a 3-minute free-form video recorded response on the Storyline platform by participants regarding perceived reciprocal effects of mindfulness training and psilocybin session.

^ix.^ Adverse event collection will occur during all 3 preparatory sessions and all 3 integration sessions for the PAP+MBSR arm. Adverse event monitoring can occur via phone contact for intervals prior to psilocybin dosing.

^x.^ If subject is rated as moderate or high risk a full C-SSRS will be completed.

^xi.^ A comprehensive metabolic panel will be done by ARUP laboratories and will be done before the start of MBSR curriculum.

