# OBJECTIVES

## Primary Objectives

### Determine the acceptability, feasibility, and safety of psilocybin-assisted therapy (PAP) plus Mindfulness-Based Stress Reduction (MBSR) for front-line healthcare worker burnout.

*Primary Endpoint:* Acceptability of each modality will be determined by ease of enrollment and retention. Feasibility will be measured by the number of enrollees who successfully complete each modality in both study arms. Safety will be measured through the monitoring of adverse events (AEs) utilizing the CTCAE (NCI Common Terminology Criteria for Adverse Events Version 5.0), suicidal ideation utilizing the Columbia Suicide Severity Rating Scale (C-SSRS), administration of the Challenging Experiences Questionnaire (ChEQ), direct participant qualitative reports, and clinician observation.

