# STUDY DESIGN

## Description

Recruitment will target physicians or nurses with at least 1 month of frontline clinical experience during the COVID pandemic who meet DSM-5 criteria for a depressive disorder, including adjustment disorder with depressed mood.

Participants that meet eligibility criteria and have a screening MBI-HSS (MP) score that meets our working definition of burnout (emotional exhaustion subscale ≥ 27) and a ‘high’ score on one other subscale (either depersonalization ≥ 13 or personal accomplishment ≤ 21) as well as a PHQ-9 depression screen ≥ 10 will be offered enrollment and following a consenting process will be randomized to either MBSR or MBSR + PAP with 12 participants per group. PHQ-9 and MBI-HSS questionnaires may be administered prior to consenting to assess eligibility. Consenting will be completed in person with paper or electronic consenting forms. The MBSR group will complete an 8-week MBSR curriculum (online) through the University of Utah Resiliency Center led by [name], LCSW which includes a weekly 2.5-hour sessions over Zoom for 8 weeks and an 8 hour in-person retreat between weeks 6 and 7. If capacity within the University of Utah MBSR groups limits enrollment and feasibility we will incorporate the MBSR programs through Intermountain as well as Davis Behavioral Health. We will run subjects through the MBSR curriculum in flexible numbers concurrently until a total of 12 have completed this arm. The MBSR + PAP group will complete this same curriculum, however will substitute an 8-hour group-format psilocybin-assisted therapy session (with 25 mg psilocybin capsule) with 1:1 therapist to participant ratio instead of the MBSR retreat day. Each participant will have an assigned individual therapist present for the duration of the psilocybin dosing session. A lead therapist ([name] PhD) will also be present for all study sessions including the psilocybin dosing day and there will be at least one lead study monitor present for the duration of the psilocybin dosing day ([name] MD or [name] MD). The psilocybin intervention will be completed in groups of 2-6 individuals per cohort. Additionally, the MBSR + PAP group will have 3, 90-minute group preparatory sessions prior to the psilocybin session and 3 subsequent 90-minute integration sessions. The first integration session will occur 1-2 days following the psilocybin session. A communal music track will be played during the PAP session. After the enrollment and treatment of the first four patients, accrual will be placed on hold to ensure participant safety. If stopping rules are not met, we will continue with enrollment.

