##### Patient-Reported Experience on Study Therapy

(COMPLETED ON STORYLINE)

Video-response questions: (administered at 2 weeks post MBSR retreat or PAP dosing session)

Please take 3-5 minutes to reflect on how you have been functioning at work, how you have been relating to patients, co-workers, and administrators, and how you have been feeling in your work environment. Note any changes in how you have been feeling or functioning. How have you felt emotionally at work?

1. Please take 3-5 minutes to describe your sense of where you are with mindfulness training. How has the retreat or psilocybin session impacted your practice? How successful have you been with daily practice? How successful have you been in integrating practice into your life even in non-formal meditation settings?
2. If you were in the psilocybin arm of the study please take 3 minutes or so to comment on your impressions of the group format for the psilocybin session. What worked, what didn't work, what would you have liked to see done differently? Please comment on format, music, group process, and anything else you think is relevant.

 Rating questions: : (administered at 2 week mark and at 2 weeks post MBSR retreat or PAP dosing session)

One question that arises in the field of psychedelic medicine is to what extent it is important for therapists to have had prior personal experience with psychedelic medicines themselves.  This is a complicated question and one that raises a number of ethical issues related to potential bias as well as problematics around personal disclosure.  Please answer the following questions as to your perceptions.

(-5 to +5 scale)

1. After your experience how important does it feel to you to have your therapist have had prior personal experience with psilocybin?

-5 -4 -3 -2 -1 0 1 2 3 4 5

1. After your experience how important does it feel to you that the study team has had prior personal experience with psilocybin?

  -5 -4 -3 -2 -1 0 1 2 3 4 5

       3. To what extent does it feel to you that prior personal experience with psilocybin among members of the study team introduces bias in a clinical trial?

  -5 -4 -3 -2 -1 0 1 2 3 4 5

Date

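### Table 2 schedules the video report on the psilocybin session and retreat in week 6, before either normally takes place, and not at the time the appendix gives (2 weeks after)

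*Protocol*

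**What the plan says.** Four places in the protocol bear on the timing of this assessment.

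- **Section 8, Table 2, assessment row.** The row "Qualitative assessment on relationship between mindfulness training and psilocybin session and group format" sits in the block of Storyline Health questionnaires and is marked in weeks 6 and 11.
- **Section 8, Table 2, treatment rows.** The PAP session and the MBSR retreat are each marked once, in week 7. The introduction to Section 8 says the schedule applies throughout the study.
- **Table 2, footnote viii.** It describes a 3-minute free-form video response "regarding perceived reciprocal effects of mindfulness training and psilocybin session". The row itself carries marker x, and footnote x is the rule for completing a full C-SSRS.
- **Appendix, Patient-Reported Experience on Study Therapy.** The video questions are "administered at 2 weeks post MBSR retreat or PAP dosing session". They ask where the participant stands with mindfulness training and daily practice, how the retreat or psilocybin session affected that practice and, in the psilocybin arm, what the participant thought of the group format.

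Two further statements govern when the events happen. Section 4.1 places "an 8 hour in-person retreat between weeks 6 and 7" for the MBSR group. Section 6.1 (MBSR+PAP Arm) adds flexibility for dosing: "this session may occur before or after the group meditation retreat +/- 1 week".

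**The concern.** The assessment looks back at an event. A team that follows Table 2 will prompt for the recording about a week before that event, and will not prompt for one at the time the appendix sets. The two instructions cannot both be followed.

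At stake is the participants' own account of the session and of the group format, which the Design Rationale presents as one of the study's innovative elements. An account not recorded about two weeks after the session cannot be collected later at that distance. The week-6 recording would give partial answers that do not serve the row's stated purpose.

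**Working it through.** **1. Are the marks really in weeks 6 and 11?** The Table 2 header has 14 cells: a label, two screening columns, then weeks 1 to 9, 11 and 33. Each row checked also has 14 cells, so there is no sign of a column shift.

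| Row in Table 2 | Weeks marked |
| --- | --- |
| Qualitative assessment, mindfulness and psilocybin session | 6, 11 |
| PAP session | 7 |
| Retreat | 7 |
| MEQ-30 (control) | 7 |
| Preparatory sessions (control) | 5, 6 |
| Integration sessions (control) | 7, 8, 9 |

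The control rows fall where the text of the protocol puts those activities.

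**2. Table against appendix, for a week-7 event.**

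- Week-6 mark: 6 − 7 = −1, one week before the event.
- Appendix time: 7 + 2 = week 9. The row has no mark there.
- Week-11 mark by column labels: 11 − 7 = 4 weeks after.
- Week-11 mark by footnote i (14 days, ± 3, after the final MBSR session in week 8): (8 − 7) + 2 = 3 weeks after, give or take 3 days.

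Neither mark matches the appendix. The first usable account comes about 3 to 4 weeks after a week-7 session instead of 2.

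**3. Effect of the one-week allowance on the PAP date.** Around a week-7 retreat, dosing could fall in weeks 6 to 8.

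| PAP session in | Appendix time (session + 2) | Delay to week-11 visit, by footnote i | Delay, by column labels |
| --- | --- | --- | --- |
| Week 6 | Week 8 | (8 − 6) + 2 = 4 weeks | 11 − 6 = 5 weeks |
| Week 7 | Week 9 | 3 weeks | 4 weeks |
| Week 8 | Week 10 (no column in Table 2) | (8 − 8) + 2 = 2 weeks | 11 − 8 = 3 weeks |

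No permitted session date makes a week-6 recording fall 2 weeks after the session. The appendix time also moves with the session, so a fixed calendar week would not reproduce it for everyone.

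**4. How many recordings.** Section 4.2 plans 24 participants, 12 per arm, and the row has two marks.

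- PAP arm only: 12 × 2 = 24 recordings, of which 12 are at week 6.
- Both arms: 24 × 2 = 48 recordings, of which 24 are at week 6.

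The protocol does not settle which applies. Footnote viii mentions only the psilocybin session, which points to one arm. The appendix wording covering retreat or session, and footnote v on similar assessment across arms, point to both.

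**5. Could week 6 be a deliberate baseline?** No text says so, and questions about the effect of a session or retreat cannot serve as a pre-event measure of it.

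**The case against.** The case for leaving this alone has several parts, and some of it stands.

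- **Part of the prompt can be answered in week 6.** The questions on mindfulness training, daily practice and its integration into life do not depend on the session. This stands. A reader might infer that the whole recording is unanswerable, but only the session, retreat and group-format parts are.
- **Dates are flexible.** Some PAP sessions could fall in week 6, and for a week-8 session the follow-up visit defined by footnote i falls about 2 weeks after dosing, as the appendix wants. So a flat 4-week delay is not supported. The contradiction still holds for the nominal week-7 schedule.
- **Safety information is gathered elsewhere.** Section 1.1 counts "direct participant qualitative reports, and clinician observation" among the safety measures, and a reader might infer that a primary safety or acceptability assessment is damaged. The protocol does not support that. Section 1.1 does not name this video, and it defines acceptability by enrolment and retention. Table 2 lists the row among the Storyline questionnaires, apart from the safety block, and Section 1.3 treats Storyline as exploratory. Around dosing, adverse events are collected in weeks 7, 8, 9 and 11, the Challenging Experience Questionnaire is given in week 7, and the first integration session follows within 48 hours.
- **It is probably clerical.** That is likely, and the wrong footnote marker on the same row suggests it. But Table 2 is what staff will work from, so the slip would change what is recorded.

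**Conclusion.** The contradiction is real and minor. As written, Table 2 calls for one of two recordings per participant before the event it asks about has normally happened, and marks none at the appendix's time. The size is 12 of 24 recordings if only the PAP arm records, or up to 24 of 48 if both do, with the session-related parts of each affected. The first usable account comes about 3 to 4 weeks after a week-7 session instead of 2. Across the permitted dosing weeks the delay runs from about 2 to 5 weeks, depending on the session date and on whether footnote i or the column label defines the visit.

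This assumes that the table columns are as counted above, that the planned 24 participants all record, and that the retreat is held in week 7 as Table 2 shows. The consequence is confined to exploratory qualitative data. Nothing here bears on the primary efficacy analysis, the sample size or the acceptability measure.

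**What to change.** Reconcile Table 2, its footnotes and the appendix:

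1. Move the week-6 mark for this row to 2 weeks after the participant's actual retreat or PAP session. This is nominally week 9, but tie it to the event date in a footnote, because the PAP date may move.
2. State whether the week-11 recording is an intended second time point. If it is, add it to the appendix, which at present gives one time only; if not, remove the mark.
3. Change the row's footnote marker from x to viii.
4. State whether one arm or both record this response.
5. While editing, check the workplace prompt. It stands under the same timing line in the appendix, but Table 2 marks it in weeks 1 and 11.

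The cost is a small edit to one table row, its footnotes and one appendix line, plus resetting the prompt date in the Storyline app. It adds no visit and, if the week-11 mark stays, no recording.
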